### Methods for additional analyses (e.g., subgroup analyses) {20b}

Subgroup analysis is not planned for the study. But in the course of the study if the investigators find something which can be used for subgroup analysis, then it will be notified to the IRC, IEC, Trial registry, and the journal too. An appropriate descriptive statistics will be used for the same.

### Methods in analysis to handle protocol non-adherence and any statistical methods to handle missing data {20c}

Sensitivity analysis will be done to handle the missing data. Missing data will be handled with multiple imputations. Per-protocol and ITT analyses will both be done.

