### Eligibility criteria {10}

The participants included in the study will be:
i.Patient: Adult patients (age > 18 years) with ASA I to II functional status undergoing elective/emergency surgical procedures under general anesthesia who can understand and provide valid consent for the procedure. The exclusion criteria will be patients less than 18 years of age, American Society of Anesthesiologists (ASA) > 2 functional status, patients having Cormack Lehane (CL) grading more than 2 on direct laryngoscopy, use of airway adjuvants, and refusal to give consent for the study.ii.Intubator: Intervention (intubation) will be performed by trainee anesthesia residents who have less than 18 months of experience. As a part of the curriculum, training in the theory of airway management and mannikin intubations will ensure that all the trainees have experience of a minimum of 40 intubations on mannikins or patients. A consultant anesthetist will supervise all intubations per protocol.iii.Procedure: All procedures will be video recorded from the time patient is positioned after induction, and the laryngoscope is asked for, to after confirmation of correct tube position (this may be visual, auscultatory, or EtCO2 guided). Procedures where the trainee deviates from the methodology, improper table position, CL grade found > 2, use of a bougie, stellate, or other airway adjuncts, or take-over by the consultant (unanticipated difficult airway), will be video recorded but excluded from the analysis. This will reduce confounding the time to intubation due to poor visualization of the laryngeal inlet.

A few cases will be tried with a Go-Pro camera, hoping to ascertain data for the exact laryngoscopy view (with the understanding that the visual axis of the camera will not be identical to the LEI, and the forehead mounted camera might make the process more cumbersome for the trainee).

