#### Dropout criteria

Any change in grip after holding the ETT, giving backward-upward-right-posterior pressure (BURP) to the larynx after holding ETT, or manipulation of the ETT like changing the curvature of the tube or rotating it by 180° will be video recorded but will be excluded from the final analysis. If any video has a conflict of opinion between the assessors regarding time to intubation or method of intubation, it will be excluded from the final analysis.

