#### Technique

After induction and a minimum of 3 min of administering the paralytic agent, the intubator will perform the laryngoscopy. Once the intubator declares that the CL grade is optimal (CL < 3), it will be confirmed by the faculty or senior either verbally or visually. Once declared as an “optimum laryngoscopic view,” the tube will be handed over by the technician to the intubator and prior instruction will be given to take the first attempt at the marked point, with the elbow close to the body, with the thumb at the plastic marker, index, and middle fingers opposite [2]. If the above will be difficult, then any change in methodology will be allowed as per the faculty’s decision and will be documented from the video. The whole procedure will be videographed.

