### Criteria for discontinuing or modifying allocated interventions {11b}

If the intubator cannot intubate at the given tube mark, he will be allowed to change the site of grip—the site change will be noted from the video. If he/she still fails, the consultant can take over.

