### Outcomes {12}

Primary outcome measures: time to intubation (TTI) in both groups. The TTI will be calculated from holding the ET to removing the laryngoscope—after declaring a tube passed “under vision.” The frame has been chosen to reduce bias due to laryngoscopy problems or delay due to attaching the circuits and ventilating till capnographic confirmation of correct tube position. The primary outcome will be described in seconds.

Secondary outcome measures assessed will be first-pass intubation success rate; intubation difficulty scores (IDS) [6]; ease of the intubation assessed by the intubator, faculty, and a blinded assessor unrelated to the study on the Likert scale (0—very easy to 5—extremely difficult); and incidence of complications (bleeding or sore throat) in each group. The IDS comprises of attempt (in no), additional operators (if any, then in no), alternative technique: stylet/bougie, Cormack Lehane grading (CL grade: I/II/III/IV), lifting force: normal (0)/increased (1), external laryngeal pressure required during insertion of the tube: no (0)/yes (1), and position of vocal cords: abducted (0)/adducted (1).

Assessments from the video footage: These assessments will be done by two different anesthesiologists independently. The mean values will be used for analysis after disputes/disagreements (if any) are settled by a third person not belonging to the research team. This will reduce bias due to possible errors in time calculations.

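### The ITT analysis of time to intubation has no sound rule for an intubation the trainee starts but never completes: dropped or imputed, the failure disappears

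*Protocol article*

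**What the plan says.** Five parts of the protocol article bear on an intubation that the trainee begins and does not finish.

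- **Outcome.** Under Outcomes {12}, "The TTI will be calculated from holding the ET to removing the laryngoscope", the removal coming after the tube has been declared passed.
- **Failure path.** Section {11b} lets a trainee who cannot intubate at the mark change grip, and then: "If he/she still fails, the consultant can take over". The Post-procedure section adds that after a failed trainee intubation the senior is assessed.
- **Exclusions.** Eligibility criteria {10} lists protocol deviations, a Cormack-Lehane (CL) grade above 2, airway adjuncts and "take-over by the consultant (unanticipated difficult airway), will be video recorded but excluded from the analysis". The Dropout criteria say that grip changes, laryngeal pressure and tube manipulation "will be video recorded but will be excluded from the final analysis".
- **Analysis population.** Section {20a} has the analysis cover every randomised patient.
- **Missing data.** Section {20c} opens with "Sensitivity analysis will be done to handle the missing data", without content, and continues: "Missing data will be handled with multiple imputations. Per-protocol and ITT analyses will both be done".

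**The concern.** An ITT analysis of TTI needs a value or a rank for each randomised patient who entered the comparison. A trainee who held the tube and did not complete has a start time and no end time. That absence is not a lost measurement. It is the worst result the allocated grip can produce.

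The protocol handles this case in ways that do not fit together. One section removes it, another turns attention to the senior's intubation, a third keeps all randomised patients, and a fourth imputes what is missing. If the failure is removed, the comparison rests on completed intubations only. If it is imputed under the usual missing-at-random model, its time is drawn from completed intubations. The ITT result is supposed to guard against the post-randomisation exclusions. Here it would repeat them while appearing to include everyone.

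**Working it through.** **Inputs from the protocol.** TTI mean 8.83 s and SD 4.07 s; a 20% difference, 0.20 × 8.83 = 1.77 s (the sample size section also names 1 s; the 20% figure is used here); 180 per arm; about 20% loss of all kinds. No rate of failed trainee intubations is given, so every rate below is an assumption.

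**Step 1: what each reading does to a failure.**

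| Reading | Value used for the failed intubation |
|---|---|
| Exclusions in {10} govern | None; completed times only |
| {20c} governs, imputed within arm | Drawn from completed times in that arm |
| Post-procedure section governs | The senior's intubation is assessed; no TTI for the trainee |

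The first two readings give essentially the same expected difference, that between completed intubations.

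**Step 2: direction.** Let m be the mean completed time, f the failure proportion, and T a long time credited to a failure (20 or 30 s, assumed). Counting failures, the difference is

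[(1 − f1)·m1 + f1·T] − [(1 − f2)·m2 + f2·T],

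while dropping or within-arm imputation gives m1 − m2. The scenarios take m1 = 8.83 and m2 = 8.83 or 7.064 (20% lower).

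| m1, m2 (s) | f1 / f2 | Dropped or imputed | Failures counted, T = 20 / 30 s | Effect of ignoring failures |
|---|---|---|---|---|
| 8.83, 8.83 | 10% / 10% | 0 | 0 / 0 | none |
| 8.83, 8.83 | 10% / 2% | 0 | 0.89 / 1.69 s | hides a difference |
| 8.83, 7.064 | 10% / 2% | 1.77 s | 2.62 / 3.42 s | toward no difference |
| 8.83, 7.064 | 2% / 10% | 1.77 s | 0.70 / −0.10 s | away from no difference |
| 8.83, 7.064 | 10% / 10% | 1.77 s | 1.59 / 1.59 s | slightly away |

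Fourth row, T = 20: (0.98 × 8.83 + 0.02 × 20) − (0.90 × 7.064 + 0.10 × 20) = 9.05 − 8.36 = 0.70 s.

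In a Mann-Whitney simulation (180 per arm, lognormal times, 3,000 runs), equal completed times with failures of 10% and 2% led to rejection in about 5% of trials with failures dropped and 27% with failures ranked worst. With a true 20% difference and the faster arm failing more (2% / 10%), the figures were over 99% and 87%.

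**Step 3: size when slowness and failure go together.** Lognormal TTI, 8.83/4.07 s in one arm and both figures 20% larger in the other (10.60/4.88 s), 180 per arm, 1,500 trials. Any intubation that would exceed a cut-off ends without a trainee TTI. Imputation is by arm on the log scale, with 10 imputations and Rubin's rules. The true difference, had all been completed, is 1.77 s.

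| Cut-off | Without TTI (faster / slower arm) | Imputed difference | Power, imputed | Power, worst rank |
|---|---|---|---|---|
| 14 s | 10% / 20% | 0.9 s | about 79% | about 96–97% |
| 16 s | 6% / 12% | 1.1 s | about 88% | about 97% |
| 18 s | 3% / 8% | 1.2 s | about 91% | about 97% |
| 22 s | 1% / 3% | 1.5 s | about 94–95% | about 97% |
| 25 s | 0.5% / 1.5% | 1.6 s | about 96% | about 97% |

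Repeat runs move power by a point or two. With complete data, power is about 96–97%. The common cut-off makes the slower arm fail more by construction, so this table shows size in that case only and is not evidence of direction.

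**The case against.** A reader might infer three stronger things, and the documents support none of them.

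- *That multiple imputation is the only written rule for a missing TTI.* It is not. Eligibility criteria {10} excludes consultant take-overs and CL grades above 2, and the Post-procedure section says who is assessed after a failure. Imputation is only the one rule that would supply a value.
- *That the plan says failures will be imputed.* No sentence classes a failed intubation as missing data. One can read {10} as removing failures and {20c} as covering, say, an unreadable video. That reading is fair, but it leaves the ITT analysis without these patients and contradicts {20a}.
- *That the bias is always toward no difference.* Step 2 shows that it can be absent or go the other way.

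Other objections have some force. Failures may be rare: the view must be CL 1 or 2 before the tube is handed over, and trainees have at least 40 prior intubations. At 0.5–3% failures the loss of power is small, although the imputed difference is still somewhat reduced. First-pass success is a separate secondary outcome, so failures would not go wholly unseen. Worst rank turns TTI into a composite of time and completion, whereas the sample size rests on a mean difference. Finally, imputation models and the content of a sensitivity analysis are commonly left to an analysis plan, and their absence here is not the point. The point is that the rules the article does state conflict over one foreseeable case.

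**Conclusion.** The concern holds in this form: the protocol promises ITT, TTI is undefined for an intubation the trainee held the tube for and never completed, and the stated rules either drop that patient or, if the absence is treated as missing, impute from successful times. In both cases the failure has no influence on the primary comparison.

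The direction of bias depends on which arm fails more. The size depends on a rate that the protocol does not give. Where slow intubations are the ones that fail, the imputed difference lies between about 0.9 s (failures 10% / 20%) and 1.6 s (0.5% / 1.5%) against a true 1.77 s. The upper failure rates are within the roughly 20% loss planned for, but that allowance covers all causes and may well overstate failures. These figures assume lognormal times and within-arm, missing-at-random imputation. The part about CL grades above 2 adds little, since {10} already leaves those patients out. The change is inexpensive and should be made before unblinded data are analysed.

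**What to change.** Revise {20c} so that it reconciles {10}, the Dropout criteria, the Post-procedure section and {20a}:

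1. State that the exclusions in {10} and the Dropout criteria define the per-protocol set only. The one exception is patients whose tube was never handed over because the CL grade was above 2: leave them out of the TTI comparison, do not impute them, and report their number by arm.
2. Limit multiple imputation to TTI lost for technical reasons, such as an unreadable video.
3. In the ITT analysis, give each intubation in which the trainee held the tube but did not complete it the worst rank, above all observed times, and compare the arms with the Mann-Whitney test already named in {20a}. The senior's time does not stand in for the trainee's.
4. Report the number of trainee non-completions by arm beside the primary result.

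Cost: wording only. The videos and case records already show why a time is absent, so no new data are needed. The downside is that the ITT effect is reported as a rank-based or median difference, not a mean difference.

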### Plans to give access to the full protocol, participant-level data, and statistical code {31c}

Reasonable access to the protocol and other documents can be made by requesting the corresponding author.

### Oversight and monitoring

#### Composition of the coordinating center and trial steering committee {5d}

Two senior anesthesiologists from the investigating team will review the adherence to the trial protocol and overall conduct of the trial every 2 months throughout the study period.

The institute research committee also oversees the regular progress of academic dissertation-based research.

#### Composition of the data monitoring committee, its role, and reporting structure {21a}

Since the study does not involve any new intervention and endotracheal intubation is a regular procedure done in operating rooms under senior anesthesiologists’ guidance, the IEC did not call for a DMC appointment.

#### Adverse event reporting and harms {22}

Endotracheal intubation is a very safe procedure, and no new intervention will be investigated.

Hence, we do not expect any unexpected adverse events to happen during the study.

#### Frequency and plans for auditing trial conduct {23}

The trial is conducted as a part of the thesis. Therefore, intermittently, there will be meetings among the researchers to find out the progress of the study as well as any lapses or modifications required in the same.

#### Plans for communicating important protocol amendments to relevant parties (e.g., trial participants, ethical committees) {25}

This study was approved by the Institutional Ethics Committee of All India Institute of Medical Sciences, Bhubaneswar, on 15 July 2019 and registered at ctri.nic.in (CTRI/2019/09/021201) on 12 September 2019.

Any modifications in the protocol pertaining to eligibility criteria, outcomes, or analyses will be discussed among the researchers first following the audit. This will be informed and approved by the Departmental academic lead, Head of the department, Institute Research Committee, and Institutional Ethics Committee. After their approval, the modifications will be uploaded to the trial registration body (CTRI). The changes especially in the eligibility criteria will also be notified to other faculty and residents so that they can notify the researchers regarding the cases as per the new protocol.

## Dissemination plans {31a}

The results obtained from this study will be disseminated at anesthesia conferences (local and international meetings). The key findings will be reported in the trial registry. After completing the study, the report will be submitted for publication in an anesthesia journal, preferably an open-access journal.

## Discussion

It is already known that the first-pass intubation rate performed by trainees depends on their years of experience. Hence, systematic training of technical and non-technical skills is essential for procedural success. As per a review in the first 100 intubations done by a trainee, the early intubations’ major problems were esophageal intubations and achieving an optimal view.

Positioning of the patient and laryngoscopy technique are the two most important factors for achieving an optimal view during direct laryngoscopy. This study will first assess the optimal site of holding ET for successful LEI when performed by the trainees. The holding site can impact the visual axes and the torque applied to the endotracheal tube. Whether this will impact the incidence of complications like bleeding and sore throat is not known.

## Trial status

This study was approved by the Institutional Ethics Committee of AIIMS, Bhubaneswar, on 15 July 2019 and was registered in CTRI on 12 September 2019. The first participant was recruited on 16 September 2019, and currently, the study is in ongoing status**.**

## Data Availability

The data generated in this study can be shared after a reasonable request to the corresponding author of the manuscript. All investigators will be having access to the cleaned data sets. The Excel sheet and video recordings will be stored electronically. These will be password protected too.

## Abbreviations

ET: Endotracheal tube
ASA: American society of anesthesiologist
IDS: Intubation difficulty score
MPG: Mallampati grading
OT: Operating theater
SD: Standard deviation
